#### Health related quality of life

The HRQOL for children and parent proxy-report will be determined by the Paediatric Quality of Life Inventory (PedsQL4.0) [70]. The PedsQL 4.0 is one of the most widely used measures of HRQOL in children and adolescents aged 2 to 18 and have proven its validity in clinical and population samples [70-72]. It has 4 generic scales (Physical, Emotional, Social, School) and consists of 23 items applicable for healthy school, as well as paediatric populations.

#### Health economic data for children

The Child Health Utility 9D (CHU 9D) [73] will be filled out by all the children in order to assess the cost-utility of the intervention. The CHU 9D is a validated measure of paediatric health-related quality of life. It has been specifically developed for use with children aged 7 to 11 years and contains 9 dimensions, each with 5 levels and it is designed to be self-completed by children. The CHU 9D will be administered at baseline, at the end of the intervention (8 months later of the baseline), 6 and 12 months post intervention.

The present questionnaire will allow for aprospective economic evaluation alongside the trial with the aim of estimating the cost-effectiveness of the NP intervention versus the CG intervention.

For collecting the resource use data and on the cost linked to the NP and CG, structured observational research methods, interviews and surveys in a sample of children will be conducted.

### Parents’ outcome

#### Anthropometric parameters

Parents’ weight and height will be measured during the children assessment appointments, following the procedures previously indicated.

#### Sedentary and physical activity behaviours

Parental sedentary and physical activity behaviours will be evaluated using the short 7-day-recall self-administered Spanish version [74] of the International Physical Activity Questionnaire (IPAQ) [74,75]. The IPAQ is one of the most widely used questionnaires of physical activity level assessment and its reliability and validity for adults has been previously established [76]. The short IPAQ allows to compute a total score of the duration (in minutes) and frequency (days) of sedentary- intensity, walking, moderate-intensity and vigorous-intensity activities. Guidelines for data processing of the International Physical Activity Questionnaire [77] will be used to analyse these questionnaires.

#### Dietary intake

To assess and monitor parents’ dietary status, the adult version of the eating frequency questionnaire (CFCA) [55] will be administered. The main difference between the adult and the children version is that parentalingestion of drinks containing alcohol will also be registered [78,79].

This questionnaire has been used previously in longitudinal dietary studies and in studies relating eating patterns and biological parameters in adults [80,81].

#### Psychological aspects

To assess the nutrition and physical exercise self-efficacy in parents, the health-specific self-efficacy scales will be used [82]. The test for the nutrition and physical exercise part has been created following the same semantic structure: “I am certain that I can do xx, even if yy (barrier)” [83]. The internal consistency (Cronbach’s alpha) for the nutrition self-efficacy scale was alpha = .87 and for the exercise self-efficacy scale it was alpha = .88 [82].

#### Health economic data for parents

The EQ-5D [84] from the EuroQol Group will be filled out by all the parents to measure the cost-utility of the intervention. The EQ-5D descriptive system comprises the following 5 dimensions: mobility, self-care, usual activities, pain/discomfort and anxiety/depression. Each dimension has 5 levels: no problems, slight problems, moderate problems, severe problems and extreme problems [85]. The EQ-5D also has the EQ visual analogue scale (EQ VAS). The EQ VAS records the respondent’s self-rated health on a vertical, visual analogue scale where the endpoints are labelled ‘Best imaginable health state’ and ‘Worst imaginable health state’ [85]. The EQ-5D has demonstrated a reliability of 0.86 to 0.90 [86]. The fill out analysis of the questionnaire will follow the user’s guide [87]. As for children, the questionnaire will be administered at baseline, at the end of the intervention (8 months later of the baseline), 6 and 12 months post intervention.

Information on resource use and on the cost associated to the part of the programme for parents (economic evaluation) will be also collected using the same structured as for children.

#### Modifier variables

It has been shown that pubertal development, socio-economic and demographic parameters, the degree of satisfaction and other factors could modulate the outcome. For that reason, a part from outcome measurements, during the study, the following control information will also be recorded.

##### Pubertal stage

Pubertal stage will be assessed by the paediatrician using Tanner criteria [88] at baseline, at the end of the intervention and during the follow-up appointments.

##### Socio-economic and demographic parameters

To control the participants’ sample for these parameters, a 10 item-questionnaire has been created. Some questions have been selected from the National Healthy Survey for children [89] and for parents [90], while some other extra questions have been designed specifically for the intervention. Briefly, all these extra questions and all the questionnaires for the intervention have been satisfactorily implemented in a pilot trial, with a similar sample of children and parents during the last edition of the Nereu programme.

##### Adherence

To control adherence rate a registerof children’s and parent’s attendance to sessions will be carried out. To consider that attendance has been satisfactory each children/parent should attend at least 80% of the scheduled sessions. Those that do not attend the 80% of the sessions will be excluded of the per protocol analysis.

##### Degree of satisfaction

At the end of the intervention, children and parents will also fill out a satisfaction survey about the intervention and the coaches.

#### Economic evaluation

The economic evaluation analysis of the cost data, the CHU-9D for the child and the EQ-5D for the parent questionnaire data and the cost-effectiveness analysis will be conducted according to the current practice methods for conducting economic evaluation. The primary cost-effectiveness outcome will be the percentage of reduction in overweight and obese children. The secondary outcome will incorporate quality adjusted life years (QALYs) as an outcome measure with the primary focus being on the impact of the child and parent quality of life, measured over a time horizon of 1 year based on the CHU-9D and EQ-5Dscore collected during the trial. The results will be expressed through the incremental cost-effectiveness ratio (ICER). The ICER is a measure that compares the difference in cost and effectiveness between the two compared interventions (NP and GC). It expresses the result as cost per QALY which can then be benchmarked against established cost-effectiveness thresholds. For example in the UK, anything costing under £20,000 per QALY is deemed cost-effective. Both parametric and non-parametric bootstrap estimates of the confidence interval for the ICERs will be estimated.

### Statistical methods

#### Management and data analysis

All data will be recorded in an electronic data sheet. Two samples will be drawn; one by intention-to-treat (ITT) and another per protocol (PPT). The ITT sample will get-together all participants assigned to each group independently of whether they complete or not the entire protocol. The PPT sample will only assemble the participants who complete the entire protocol. The analysis of the results will be carried out according to the statistical analysis plan.

#### Statistical analysis plan

An initial data analysis to debug and validate the data entered in the dataset will be performed. To assess the comparability of baseline characteristics between study groups, chi-square test (or Fisher’s exact test) for nominal variables and Student’s *t* test (or the Mann–Whitney test) for continuous variables will be used.The evolution of the quantitative efficacy parameters will also be assessed, by group, for the different time periods, using a repeated measures analysis (at Baseline, 9, 15 and 21 months; see Table 1). In the case of a homogeneity violation in any relevant variable of the study groups, the multivariate analysis will be performed (Multiple regression analysis). The percentage of participants who reach to reduce their BMI SD score per study group will be evaluated, also by logistic regression models. For this analysis, the estimations will be adjusted by baseline factors such as demographic and predictive factors for the other dependent variables. As a sensitive analysis, unadjusted estimates will also be presented in different scenarios to assess the robustness of the results. The 95% confidence interval will be estimated for all parameters. Statistical analysis will be performed using the Statistical Package for Social Sciences SPSS v17 and the level of significance will be set to 5%.

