### Randomization

On a first phase, professionals of the HCP in Lleida are informed of the purpose and the methodology of the study and are invited to participate in it. Sixteen HCPs accepted to cooperate in this study. Each HPU is responsible for the recruitment of participants and for the checking of their eligibility. Randomization will be centralized at the Primary Care Research Institute (IDIAP) Jordi Gol in Lleida. Each cooperating healthcare paediatric unit (HPU) will provide a random list of their patients/children fulfilling age and BMI SD scores inclusion criteria according to the data from their health clinical records. These eligible children will be randomly assigned to one of the study groups. Randomization will insure that patients are distributed to the 2 groups homogenously in terms of age and gender. Group homogeneity with regard to age will be assured by stratified randomization according to the age group: 6,7,8,9,10,11,12 years old (7 groups) in each HPU (16 HPU).

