### Recruitment strategy

Next, each HPU will phone/contact eligible families and will invite them to participate in the study. At that point participants will be informed about their study/case group. HPUs will recruit participants consecutively and on an alternate list mode basis, i.e. once they have recruited one eligible child from the intervention group list, they move on to recruit another participant from the CG list. Families of eligible children that accept to participate will be referred to their healthcare paediatric unit office for anin-depth explanation, followed by a medical assessment (basic exploration and blood test to check for inclusion and exclusion criteria). Children’s assent and written parental informed consent will be obtained from children who fulfil the inclusion criteria and with no exclusion criteria. The family will be finally included in the study.

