### Sample size

The aim of the research team is to recruit 50 subjects per group, computing a total of at least 100 participants. The calculation of the sample size takes as its primary outcome intervention efficacy - the reduction of BMI SD scores after the intervention, as specified in a published meta-analytic review of trials [24]. The sample size was calculated in order to detect one BMI SD scores reduction (effect size = 0.60 [24]), according an 80.0% statistical power, 5% significance level to detect differences between groups with two independent samples. It is assumed a 20% dropout rate was estimated.

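### Covariates enter the quantitative analysis only after a baseline imbalance, so the HPU, within which the trial stratifies and alternates arms, will rarely enter; naming it is a small, nearly free gain

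*Protocol article*

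**What the plan says.** The Randomization section of the Protocol article describes "stratified randomization according to the age group: 6,7,8,9,10,11,12 years old (7 groups) in each HPU (16 HPU"). That is 7 × 16 = 112 strata for about 100 children. Under Recruitment strategy, "HPUs will recruit participants consecutively and on an alternate list mode basis": after a child from one arm's list, the HPU turns to the other arm's list. Contacted children are therefore close to 1:1 within every HPU.

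The Sample size section does not use this restriction. It is set up "to detect differences between groups with two independent samples".

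The Statistical analysis plan section does not use it either. For the quantitative outcomes it says "The evolution of the quantitative efficacy parameters will also be assessed, by group, for the different time periods, using a repeated measures analysis", and it gives one route for adding variables: "In the case of a homogeneity violation in any relevant variable of the study groups, the multivariate analysis will be performed". The logistic analysis of BMI SD score reduction has its own, open list: "the estimations will be adjusted by baseline factors such as demographic and predictive factors for the other dependent variables". HPU is not named in any of these. Intervals are promised throughout: "The 95% confidence interval will be estimated for all parameters".

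**The concern.** When a trial balances its arms within a factor, differences between the levels of that factor largely cancel from the treatment difference. An analysis that leaves the factor out still counts those differences as residual noise. The reported standard error is then larger than the true one, the test rejects less often than its nominal 5% under the null, and some power is lost.

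The plan does more than leave the matter open. It fixes a rule under which covariates enter the quantitative analysis only after an imbalance. Such a rule tends to pass over the factors that the design has balanced, and HPU is the clearest of these. The loss would fall on a trial whose power is already modest.

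**Working it through.** **Inputs.** From the article: 16 HPUs (Randomization); 50 per group, standardised effect 0.60, 5% level, 80% power and 20% dropout (Sample size); NP groups of at most 15 (Intervention, Nereu programme). Assumed because the article does not give them: two-sided testing, an HPU ICC between 0 and 0.20, and a correlation of 0.7 between baseline and follow-up. The Sample size section also calls its effect a one-point reduction ("detect one BMI SD scores reduction (effect size = 0.60 [24"]); the 0.60 is used here as the standardised effect.

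**1. The plan's own figure.** n = 2(1.960 + 0.842)² / 0.60² = 43.6, so 44 per group. For 20% dropout, 44/0.8 = 55, or 44 × 1.2 = 52.8, so 53. The stated 50 is not reproduced, which is a separate matter. It does show the power available: 50 × 0.8 = 40 completers per group give Φ(0.60/√(2/40) − 1.960) = Φ(0.723) = 76.5%.

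**2. HPU left out, one time point.** Take total variance 1, with a share ICC lying between HPUs. With exact balance the HPU terms cancel, so the true variance of the difference is 2(1 − ICC)/n, while the analysis without HPU estimates about 2/n.

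- Reported SE / true SE = 1/√(1 − ICC)
- True type I error = 2[1 − Φ(1.960/√(1 − ICC))]

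Two simulations check this. Both use 16 HPUs (4 of size 7 and 12 of size 6, total 100) with arms alternating within HPU. One keeps all 100 children (8,000 runs). The other keeps 80 random completers (20,000 runs), so dropout erodes the balance.

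| ICC | Formula: SE ratio, type I error | 100 children: SE ratio, type I error | 80 completers: SE ratio, type I error |
|---|---|---|---|
| 0 | 1.000, 5.0% | 0.99, 5.3% | 0.223/0.223 = 1.00, 4.9% |
| 0.05 | 1.026, 4.4% | 1.03, 4.2% | 0.223/0.220 = 1.01, 4.6% |
| 0.10 | 1.054, 3.9% | 1.04, 4.2% | 0.223/0.214 = 1.04, 4.0% |
| 0.20 | 1.118, 2.8% | 1.10, 3.2% | 0.222/0.207 = 1.07, 3.5% |

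**3. Change from baseline.** The planned analysis follows outcomes over time, so the group-by-time contrast matters most. An HPU effect that is constant over time cancels from it. With level ICC 0.05 to 0.20 and all 100 children, the SE ratio was 0.99 to 1.01 and the type I error 4.7% to 5.2%. When HPUs also differed in change (variance share 0.05), the ratio was 1.03 and the type I error 4.2%.

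**4. Clustering in the other direction.** Children in the NP arm are treated in groups. With groups of 15 in that arm only, true SE / reported SE = √((2 + 14 × ICC)/2). A group ICC of 0.01, 0.05 or 0.10 gives 1.03, 1.16 or 1.30. If the HPU and group ICCs were equal, the net ratio would be √((1 − ICC) + 7 × ICC): 1.14 at 0.05 and 1.26 at 0.10.

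**5. What adding HPU does to power.** Effect 0.60, 80 completers, one time point. The two forms were simulated separately (20,000 runs with fixed effects, 6,000 with a random intercept).

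| ICC | Fixed effects: without → with HPU | Random intercept: without → with HPU |
|---|---|---|
| 0 | 74.7% → 72.4% | 75.2% → 75.8% |
| 0.05 | 76.1% → 75.4% | 76.9% → 78.5% |
| 0.10 | 76.7% → 77.8% | 76.3% → 79.1% |
| 0.20 | 76.9% → 81.5% | 77.1% → 82.9% |

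Type I error with the random intercept was 5.2–5.4%, slightly above 5%, using a generous 78 degrees of freedom. With about 6 children per HPU (100/16 = 6.25), the random intercept is the form that loses nothing at ICC 0.

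**The case against.** The case against has several parts, and most of it limits the point.

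- **The planned analysis is longitudinal.** The widening in step 2 belongs to a single-time comparison. This stands: for change from baseline it disappears unless HPUs differ in change.
- **Other structure acts the other way.** NP group clustering (step 4) is also unmodelled. In addition, only the counselling arm is treated by the HPU's own nurse or paediatrician (Counselling group section), so part of any clinician effect is not shared between arms and does not cancel. With about 2.5 completers per HPU per arm, the design effect in that arm is 1 + 1.5 × ICC. The SE of the difference then rises by √((2 + 1.5 × ICC)/2), which is 1.04 at 0.10 and 1.07 at 0.20. A common HPU intercept would not capture this. The objection stands as to net width, but it does not argue for ignoring the restriction.
- **The list is open and the article is condensed.** The adjustment list is illustrative, and a fuller plan may name HPU. Exclusions after contact and dropout can also unbalance HPU, so it could occasionally enter. This stands in part. The list is attached to the logistic analysis, however, and for the quantitative outcomes the article states a rule based on imbalance.
- **Any error from this source alone is conservative.** This stands and keeps the severity low.

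A reader might infer that the trial's confidence intervals will come out too wide. The documents do not support that. They report no between-HPU variance, the effect largely vanishes for change from baseline, and NP clustering could make the intervals too narrow overall.

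**Conclusion.** The point holds as a low-severity, free improvement. The trial stratifies and alternates within HPU, while the stated rule for the quantitative outcomes will rarely bring HPU into the model. If outcomes differ between HPUs, the test at a single time point is mildly conservative: the SE is about 4–5% too wide with type I error near 4% at ICC 0.10, and 7–12% too wide with type I error of 2.8–3.5% at ICC 0.20. If only levels differ and stay constant over time, change from baseline is essentially unaffected.

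These sizes rest on assumed ICCs, near-balance within HPU, random dropout where dropout was simulated, and HPU effects common to both arms. The net width of the reported intervals cannot be determined from the article.

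**What to change.** In the Statistical analysis plan section, state that the between-arm models for BMI SD score and the other quantitative outcomes include HPU as a random intercept and age as one continuous covariate, whatever the baseline comparisons show. Apply the HPU term to follow-up or change values. If baseline is one of the modelled time points, an intercept that is constant over time does not bear on the group-by-time contrast. Do not model the 112 HPU-by-age cells.

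For the logistic model the term is optional: the odds ratio becomes conditional on HPU, and its interval need not narrow.

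The cost is one sentence and a slightly more complex model. HPU and age are known for every child. In the simulation the random intercept lost no power when HPU explained nothing, whereas 16 fixed effects cost about 2 points. Degrees of freedom should be chosen with care, given the type I error of 5.2–5.4% above. This change does not deal with clustering in the NP groups, which needs its own provision.

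### Adjustment of the continuous outcomes, BMI SD score included, is made to depend on a baseline imbalance instead of being fixed in advance

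*Protocol article*

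**What the plan says.** All statements on the analysis are in the Statistical analysis plan section of the protocol article.

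- Baseline tests come first: "To assess the comparability of baseline characteristics between study groups, chi-square test (or Fisher’s exact test) for nominal variables", with Student's t or Mann–Whitney tests for continuous variables. The significance level is 5%.
- For the continuous outcomes: "The evolution of the quantitative efficacy parameters will also be assessed, by group, for the different time periods, using a repeated measures analysis". Baseline is listed as one of the four time points.
- The adjustment rule follows: "In the case of a homogeneity violation in any relevant variable of the study groups, the multivariate analysis will be performed". Multiple regression is named as the method. The relevant variables and the covariates are not listed.
- For the binary version: "The percentage of participants who reach to reduce their BMI SD score per study group will be evaluated, also by logistic regression models". This model is adjusted for baseline factors without any condition, and unadjusted estimates serve as sensitivity analyses.

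The Sample size section takes as primary outcome "the reduction of BMI SD scores after the intervention", compared between two independent groups. The Randomization section stratifies by seven age groups within each of 16 paediatric units.

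**The concern.** The rule makes the model for the sized outcome depend on the data. Two things are wrong with that.

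1. **The trigger is the wrong one.** Under randomisation a baseline difference arises by chance. A covariate deserves adjustment because it predicts the outcome, whether or not it happens to differ between arms. Baseline BMI SD score can be expected to predict later BMI SD score, and it is collected anyway.
2. **The rule leaves room for choice.** With no list of relevant variables or covariates, whether to adjust, and for what, is decided after the data are seen.

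At stake are the credibility of the main treatment estimate and some precision in a trial of about 100 children. An unseen full plan does not remove the point, because the article states the rule itself.

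**Working it through.** **1. The plan's own sample size.** Inputs from the Sample size section: effect size 0.60 (taken as standardised, SD = 1), power 80%, 5% level (taken as two-sided), 20% dropout, 50 per group.

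n = 2(1.96 + 0.84)² / 0.60² = 43.6, so 44 per group; 44 / 0.8 = 55 after dropout, or 53 if inflated by 1.2. The stated 50 is not reproduced, which is a separate matter. Here it only fixes the number of completers: 50 × 0.8 = 40 per arm. Unadjusted power is then Φ(0.60 × √(40/2) − 1.96) = Φ(0.72) = 76.5% (75.5% with the t distribution).

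**2. How often chance fires the trigger.** For k independent baseline tests at 5% with no true imbalance, P(at least one significant) = 1 − 0.95^k:

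| k | 1 | 5 | 10 | 15 |
|---|---|---|---|---|
| P | 5% | 23% | 40% | 54% |

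Table 3 lists well over 15 measures. Many are correlated, so these figures are indicative. They show that the outcome of the rule turns on how many variables are called relevant.

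**3. What always adjusting gains.** The outcome is a reduction and baseline is a time point in the repeated measures analysis, so the fair default is the change score. With equal SD σ at both visits and correlation r (not in the document, so a range is assumed):

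- variance of change: 2(1 − r)σ²
- residual variance after adjustment for baseline (ANCOVA): (1 − r²)σ²
- ratio: (1 + r)/2 = 0.75, 0.85, 0.90, 0.95 at r = 0.5, 0.7, 0.8, 0.9

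Simulation: 10,000 trials per setting, 40 per arm, true effect 0.60 SD of change. The rule uses the change score unless baseline differs at p < 0.05, and then uses ANCOVA.

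| r | Power, triggered rule | Power, always ANCOVA | Gain (points) | Type I error, triggered rule |
|---|---|---|---|---|
| 0.5 | 76.5% | 86.4% | 10 | 4.4% |
| 0.7 | 75.7% | 80.9% | 5 | 4.8% |
| 0.8 | 75.6% | 79.0% | 3 | 4.5% |
| 0.9 | 75.0% | 76.5% | 2 | 5.0% |

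With an assumed effect of 0.3 SD of the follow-up score, the rule against always-ANCOVA gives 41 v 46%, 56 v 60% and 84 v 86% at r = 0.7, 0.8, 0.9. Across these settings and simulation error, the gain is roughly 1 to 6 points for r from 0.9 to 0.7.

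**4. If the default ignored baseline.** With follow-up values only, an effect of 0.60 SD of the follow-up score and r = 0.5, 0.7, 0.9, the rule has power 77, 78, 79% against 86, 96 and about 100% for always-ANCOVA. Its type I error is 4.3, 3.5, 2.3%. The loss is much larger, but the test becomes conservative, not liberal.

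**The case against.** **Homogeneity may mean equal variances.** The phrase allows it. But the sentence speaks of variables of the study groups, comes shortly after the tests of baseline comparability, and offers multiple regression as the remedy. The baseline reading is the more natural one, though it remains an inference.

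**Little is lost and no false positives are created.** This stands. With a change-score default the power loss is small, and type I error is at or below 5%. A reader might infer a large power loss by setting the rule against follow-up values alone. The documents point away from that, because the primary outcome is a reduction and baseline is in the repeated measures analysis.

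**Stronger readings go beyond the text.** A reader might infer any of the following:

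- The conclusion will rest on change within each arm. But an analysis by group over time can be a group-by-time model, and both the aim and the Sample size section compare the arms.
- The dichotomy has become the main analysis. But the logistic model is introduced as an addition, and the continuous outcome is the one that was sized.
- Children missing one visit will be dropped. But the repeated measures procedure is not specified.
- Success may be claimed at any visit. No section says so.

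**All covariate adjustment is conditional.** It is not: the logistic model is always adjusted, although its covariates are given only as examples.

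**Conclusion.** The concern holds for the quantitative outcomes, BMI SD score among them, and not for the logistic model. As written, chance imbalance and judgement about relevance decide whether the comparison is adjusted and for what. The main harm is a model chosen after seeing the data. The secondary harm is lost precision: roughly 1 to 6 power points at r = 0.9 to 0.7, and about 10 at r = 0.5.

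These sizes assume 40 completers per arm, equal SD at both visits, a change-score default, an effect of 0.60 SD of change (a similar range at 0.3 SD of the follow-up score for r = 0.7 to 0.9), and a trigger on baseline BMI SD score alone. They do not support a claim of inflated type I error. The point is worth correcting because the remedy is nearly free, not because the planned analysis would be invalid.

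**What to change.** - Remove the baseline significance tests as a trigger, and show baseline characteristics descriptively only.
- Prespecify one intention-to-treat comparison of BMI SD score at the end of the intervention, as Nereu minus Counselling with a 95% confidence interval. Always adjust it for baseline BMI SD score and age. Include paediatric unit as a random effect if it can be estimated: 7 × 16 = 112 strata for about 100 children rule out adjusting for every stratum.
- A linear mixed model using all available visits, with group, visit and their interaction, would deliver this contrast. It is one suitable choice among several.
- Treat the later visits as secondary and the logistic model for any reduction as supportive, with its covariates listed.

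The cost is a change of wording before unblinded data are seen. The covariates are already collected, and SPSS, the package named in the plan, can fit a mixed model.
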